
### Socio-demographic questionnaire

Demographic and background information on families will be collected at baseline from parents and will include the physical and mental health of family members, perceived social support, and socioeconomic status (assessed using information on parental income, employment, education, and living circumstances). The questionnaire will provide important data for purposes of attrition analysis and for testing the equivalency of the control and intervention groups. A brief follow-up version will be used to assess any changes at 6- and 12-month follow-up (e.g. change of partner, new children)

### Process evaluation

The process evaluation will run in parallel to the RCT and will involve the application of mixed methods to investigate the experiences and contextual factors related to receiving/implementing FT. The analysis will be informed by the MRC guidance for complex interventions [35] and will be located within an implementation science framework (e.g. Fixsen’s implementation model [48]). The quantitative and qualitative elements of the process evaluation are outlined below.

#### Quantitative element: survey and questionnaire

A *Family Satisfaction Questionnaire* will ask families (parents and children) to assess their experience of FT following the intervention. The parent version of the questionnaire has 18 items and the child version has 12 items. Participants will be asked to evaluate the extent to which FT was a positive experience for families, helped with family functioning and understanding of mental health, and to provide suggestions for improvement.An online Qualtrics survey will be administered to clinicians following FT delivery in order to assess implementation fidelity. The survey takes approximately 15 min to complete and assesses clinician adherence to session checklists as well as family attendance and engagement to the intervention.

#### Qualitative element: interviews and focus groups

##### Interviews with parents and partners

Semi-structured interviews will be conducted with a subsample of parents (*n* ≈ 15–20) and partners (*n* ≈ 10) involved in the RCT in order to explore their experience of participating in FT and to learn to what extent it met their needs. A maximum variation sampling strategy will be employed in order to recruit a heterogeneous sample across different site locations and with different demographic characteristics (e.g. age, marital status, socioeconomic status). Interviews will be conducted at 6- and 12-month follow-up. Interviews will take place in the participant’s home/site centre or remotely (phone/video call) and will last approximately 20–40 min. A brief interview will also be carried out with parents who dropped out of FT before completion (*n* ≈ 10) to assess their reasons for attrition.

##### Interviews with children

Semi-structured interviews (15–30 min) will also be conducted with a small sample of children aged 12–18 years (*n* ≈ 10) at 6-month follow-up in order to explore their experience of the FT programme and the extent to which they think it helped them and other family members.

An alternative interview story approach will be used to interview younger children (8–11 years) (*n* ≈ 8–10). The interview story (15–30 min) involves a family imagined by the child in which a parent has mental health difficulties. The child is encouraged to build up a picture of the house, location, and family members who live in the home. Picture cards are used to help the child identify emotions. The child is also asked to imagine that the family attends FT and to relate the family’s experience of the programme (e.g. what helped, what could be improved). The interview story approach has been used successfully in previous research [49] to discuss sensitive issues with younger children (e.g. children who have experienced domestic abuse). The indirect approach allows the child to externalise the issue and talk about it in a more objective fashion, thereby offering emotional protection to the child. Occasionally, children may slip into ‘I’ language during the course of an interview rather than use the name of the character they have chosen. If that happens, the researcher mirrors the language used by the child. Ethical issues in interviewing children are outlined later.

##### Interviews/focus groups with clinicians, managers, and policymakers

One-to-one semi-structured interviews and/or focus groups will be conducted with FT clinicians/service providers across all participating sites (*n* ≈ 20). Individual interviews will last 30–60 min and focus groups will last approximately 60–90 min. This will cover topics such as the experience of implementing and delivering FT within services; key outcomes and enablers and barriers to delivery; rates of recruitment and attrition and organisational support, amongst other issues.

A small number of in person/phone/video call interviews (15–30 min) will also be held with managers/decision makers within sites where possible (e.g. Area Managers, Executive Clinical Directors, consultant psychiatrists) (*n* ≈ 10). The purpose of the interview will be to elicit their experience/views of FT within their service and to assess to what extent the intervention fits with their policy and practice objectives.

### Cost-effectiveness analysis of family talk

A Service Utilisation questionnaire (SUQ) and cost diaries will be used to conduct a cost-effectiveness analysis of Family Talk compared to usual services on our primary outcome measures. The SUQ is an adapted version of the Client Service Receipt Inventory [50] and has been used in previous research [51, 52]. The form will assess the type and number of contact families have had with healthcare, social care, and educational services in the previous 6 months and will be completed at baseline and at 6-month follow-up. The form will be administered by means of a face-to-face interview carried out by researchers with parent participants, along with the other psychometric inventories outlined above.

Cost diaries will be administered to programme facilitators asking them to document the time taken to train in FT, recruit and engage families, and deliver the programme, materials, and costs incurred. Time will be multiplied by salary/wage costs to calculate the approximate cost of delivering FT.

### Participant timeline

The flow of participants from recruitment through to the end of the study is shown in Fig. 2. Parents and children will be assessed at T0 (pre-intervention), at 6-month follow-up (T1; 3 months post intervention), and at 12-month follow-up (T2). Assessment of the control group will continue up to T1, after which they will be offered FT. Assessment of the intervention group alone will continue at 12-month follow-up. Enrolment into the study will be on a staggered basis and will depend on clinicians referring suitable families to the research team.

Data collection and delivery of the intervention were necessarily paused for 4 months (mid-March to mid-July 2020) due to the COVID-19 lockdown restrictions in the RoI. Therefore, assessments affected by the restrictions will be collected 4 months later than originally planned. However, taking the pause into account, we still consider the assessment time points to be 6- and 12-month follow-up. Assessments affected by the COVID-19 suspension will be noted in the analysis.

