### Waitlist control group

Families assigned to the control group will receive treatment as usual, i.e. the parent with mental illness will receive medication/psychotherapy from their psychiatrist/MDT/GP. The only difference in service utilisation between the intervention and control group will be that the former will receive Family Talk 6 months earlier. A Services Utilisation Questionnaire will be used to document the types of service supports received by control and intervention group families between T0 and T1 (i.e. baseline to 6-month follow-up).

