### Recruitment

The recruitment phase opened in March 2019 and closed on 30th November 2020 to allow sites time to recruit a sufficient sample of suitable families to the research. Unfortunately, the funding timeline means that we cannot further extend the enrolment period in order to account for the 4-month suspension caused by the COVID-19 lockdown restrictions, and as such, recruitment rates will be affected. As indicated above, the early phase of the current study involved a prior installation and implementation period in order to allow sites to train and gain experience in delivering FT [9]. Families (parents and children 5–18 years) will be recruited by clinicians in each site from their existing waiting lists. Recruitment brochures and posters will be used to inform families and clinicians about FT and the PRIMERA research. In addition, each site has nominated a lead contact person who will take responsibility for promoting FT and the PRIMERA research within their area in order to encourage referrals.

Clinicians will meet with families to assess their suitability for FT and the research process using the eligibility criteria outlined above. Once the clinician has secured agreement from the parent that they are interested in participating, they will ask for their written consent (on the family recruitment leaflet) for their contact details to be passed in confidence to the research team. Parents will then be contacted by the research team via telephone to arrange for one of the research team to talk to them in more detail about the study and to arrange to visit them to tell them more about the research and obtain their written informed consent in person. Two children per family—aged 8–18 years—are eligible to participate and their written assent will be obtained once their parent has provided prior consent for their child’s participation. Written informed consent/assent will be obtained at each data collection time point, and also if a parent/child is asked to participate in a qualitative interview. Families will be incentivised to participate with a shopping voucher worth €20 at each data collection visit. Families will be informed within 2 weeks about their allocated group.

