#### Economic evaluation

The economic evaluation will compare the cost-effectiveness of receiving FT versus a services as usual control group on our primary outcomes at 6-month follow-up. The cost-effectiveness analysis CEA will be undertaken in three key steps:
(i)Identify the cost of delivering FT, obtained through cost diaries completed by service providers(ii)Compare service utilisation for the intervention and control groups conditions (completed by parents on the Services Utilisation Questionnaire at baseline and 6-month follow-up); and(iii)Calculate an incremental cost-effectiveness ratio (ICER) to give the cost of obtaining a one unit decrease on the clinical outcome measures employed in the RCT (i.e. SDQ, SCORE-15) when comparing FT to usual services at 6-month follow-up.

The ICER will use a 1000 replication bootstrap to provide a 95% confidence interval accompanied by appropriate sensitivity analyses (e.g. excluding non-recurrent costs of training). The ICER accommodates sampling (or stochastic) uncertainty and varying levels of willingness to pay for reductions in the primary outcomes of interest. The CEA will adopt a multiagency, public sector, analytic perspective and will use official sources (e.g. government pay scales, the Casemix/HIPE unit of the Health Service Executive) to provide estimates of unit costs separate from frequencies of resource utilisation.

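### For families whose T1 visit the COVID-19 pause moved to about month 10, the fixed 6-month service-use recall leaves months 0–4 unrecorded, so the service costs in the ICER cover the wrong window (minor)

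*Protocol article*

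**What the plan says.** All places are in the protocol article.

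- **Participant timeline.** "Data collection and delivery of the intervention were necessarily paused for 4 months (mid-March to mid-July 2020"), and "assessments affected by the restrictions will be collected 4 months later than originally planned". The labels are kept: "taking the pause into account, we still consider the assessment time points to be 6- and 12-month follow-up". Affected assessments are to be flagged when the data are analysed; no other handling is given.
- **Cost-effectiveness analysis of family talk.** The service-use form records contacts "in the previous 6 months and will be completed at baseline and at 6-month follow-up".
- **Waitlist control group.** The same form is said to document the supports "received by control and intervention group families between T0 and T1 (i.e. baseline to 6-month follow-up").
- **Economic evaluation.** Step (ii) is to "Compare service utilisation for the intervention and control groups conditions", using the baseline and T1 forms. Step (iii) forms the ICER "when comparing FT to usual services at 6-month follow-up". The cost of delivering Family Talk comes separately, from provider cost diaries.
- **Recruitment.** "The recruitment phase opened in March 2019 and closed on 30th November 2020".

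**The concern.** A 6-month recall asked at T1 covers the whole T0–T1 interval only if T1 falls at month 6. A T1 visit held 4 months late no longer reaches back to baseline, and keeping the 6-month label does not change that. The pause stopped data collection and Family Talk delivery. It did not stop calendar time, and the article does not say that it stopped usual care from the psychiatrist, team or GP.

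Cost-effectiveness is one of the trial's principal aims. Under the rules as written, unmoved families contribute service costs for their whole T0–T1 interval. Moved families contribute a 6-month cost that starts 4 months after baseline and may fall largely in lockdown. Flagging these visits cannot recover months that nobody was asked about.

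**Working it through.** **Inputs.** Recall length is 6 months, with forms at baseline and T1 (Cost-effectiveness analysis). Planned T1 is month 6, and the delay for affected visits is 4 months (Participant timeline). The period to be documented is T0 to T1 (Waitlist control group).

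**1. Coverage.** The baseline form covers months −6 to 0. The T1 form covers T1 − 6 to T1. The unrecorded part of T0–T1 is max(0, T1 − 6).

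- As planned, T1 = 6: the form covers months 0–6 and the gap is 0. This reproduces the coverage that the article states.
- Moved, T1 = 6 + 4 = 10: the form covers months 4–10 and the gap is months 0–4. Share: 4/10 = 40%.
- If the real delay were 1, 2 or 3 months, the gap would be 1/7 = 14%, 2/8 = 25% or 3/9 = 33%.

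**2. How much of each window lies in the pause.** Put the pause at calendar months 0 to 4 and baseline at B. The lost months run from B to B + 4 and the recalled months from B + 4 to B + 10.

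| B | Lost months in the pause (of 4) | Recalled months in the pause (of 6) |
|---|---|---|
| −6 | 0 | 4 |
| −5 | 0 | 4 |
| −4 | 0 | 4 |
| −3 | 1 | 3 |
| −2 | 2 | 2 |
| −1 | 3 | 1 |
| 0 | 4 | 0 |

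T1 was due in the pause for B from −6 to −2 (enrolled mid-September 2019 to mid-January 2020). For these families 2–4 of the 6 recalled months are paused months. For B from −2 to 0 (enrolled mid-January to mid-March 2020), T1 was due after the pause ended. The article does not say whether those visits were moved as well. If they were, 0–2 of the recalled months and 2–4 of the lost months are paused months.

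**3. How many families might be affected.** The article gives no count. *Assumption:* no enrolment during the pause. March 2019 to November 2020 is 21 months, and 21 − 4 = 17 open months. Let r be the enrolment rate in the affected months relative to the other open months. The share affected is p = 4r/(4r + 13) for the 4-month group, or p = 6r/(6r + 11) if the later two months are included. Excluding a share p widens a confidence interval for a mean by about 1/√(1 − p).

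| r | 4-month group: share, width factor | 6-month group: share, width factor |
|---|---|---|
| 0.5 | 2/15 = 13%, 1.07 | 3/14 = 21%, 1.13 |
| 1 (even enrolment) | 4/17 = 24%, 1.14 | 6/17 = 35%, 1.24 |
| 2 | 8/21 = 38%, 1.27 | 12/23 = 52%, 1.45 |

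The width rule is for a mean. A bootstrap interval for a cost-effect ratio need not scale in this way.

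**The case against.** The strongest reply is that no harm to the ICER has been shown. Every family, moved or not, contributes a service-use window of the same length. Randomisation is blocked and stratified by site, so moved families should fall in both arms in about the allocation ratio. Family Talk delivery is costed from diaries, not from this form. If the target is a 6-month cost and the monthly difference between arms is constant, months 4–10 give the same difference as months 0–6. All of this stands, and it sets the severity.

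A second reply is that the article's list of sensitivity analyses is open-ended, and that the way an interviewer anchors recall at a late visit may be fixed in the full protocol or the instrument. Field practice may indeed have differed. But the article states the recall length, the form timing and the delay, and it reports protocol version 4, dated 06.08.2020, after the pause had ended. Nothing in it changes the recall. A later sensitivity analysis also cannot restore unasked months.

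A third reply is that lengthening recall for moved families only makes recall error differ between moved and unmoved families. That is a real trade-off.

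Two stronger readings are tempting. A reader might infer that the ICER is biased or that costs are understated; for the reasons in the first reply, the documents do not show this. A reader might also infer that the lost months are those in which the sessions were delivered before lockdown. The article gives no start date for session 1. It places T1 three months after the intervention, so planned delivery ends near month 3, and families enrolled after mid-December 2019 would then have run into the pause. The sessions are costed from the diaries in any case.

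**Conclusion.** The point holds as a minor one. For each moved family, 4 of the 10 months between T0 and T1 (40%) are in neither form, and the statement that the form documents T0 to T1 fails. Month-10 outcomes are set against service costs from months 4–10. The gap rests on the article's own rules being followed literally, with a delay of the full 4 months. The shares of families affected rest on the enrolment assumptions shown, because no count is given. The finding is lost data and a mismatched cost window. Neither the direction nor the size of any effect on the ICER can be obtained from the document.

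**What to change.** At T1 visits still to be held late, start the service-use recall at the baseline date and record months 0–6 and 6–10 separately. A common 6-month cost and the full T0–T1 cost can then both be formed. Report the actual number of months from T0 to T1.

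For moved visits already held, add one sensitivity ICER that excludes families by enrolment date: mid-September 2019 to mid-January 2020, or to mid-March 2020 if those T1 visits were also moved. Enrolment date is fixed before randomisation, so the arms stay comparable.

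The cost is a 10-month instead of a 6-month recall, with more recall error, for moved families only, plus one extra and less precise ICER. Under even enrolment the exclusion drops 24% or 35% of families and widens an interval for a mean by about 14% or 24%. With enrolment in those months at half to double the rate of the others, the ranges are 13–38% dropped (7–27% wider) and 21–52% dropped (13–45% wider).

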### Sample size

A power analysis was conducted using the two primary outcome measures—the Strengths and Difficulties Questionnaire (SDQ) and the Systematic Clinical Outcome and Routine Evaluation (SCORE-15)—in order to identify the minimum sample size required to detect an improvement in child and family psychosocial functioning post intervention.

Three of the previous RCTs of FT employed intensive clinician interviews to assess child psychosocial functioning and reported statistically significant results with varying sample sizes (*n* = 28–105) [23–25]. Similar to two previous evaluations of FT [26, 27], this study intends to use the brief SDQ to measure child psychosocial functioning. These studies reported effect sizes of 0.70 and 1, respectively, at post intervention. The Finnish study [26] involved 109 families and the German study [27] recruited 37 families. The power calculation for the current study was conducted for an independent samples *t*-test, as this is expected to be the least powerful test in the overall main analysis. Using G*Power *t*-test calculations for the difference between two independent means (two groups), and assuming *α* = .05, 80% power, two tailed testing, 15% attrition, and 2:1 allocation, the study will need to recruit 38 participants (FT = 25, TAU = 13) to detect a change between 0.7 and 1. Given that the effect sizes in these two studies are large, we intend to recruit additional families to enable us to detect smaller changes, where they exist.

Family functioning has not been typically assessed in previous evaluations of FT despite the fact that enhanced family communication and cohesion are key intervention goals. One previous study has assessed family functioning using intensive clinician interviewing of families [25], although it should be noted that two ongoing evaluations of FT have included it as an outcome, albeit using measures that take considerably longer to administer than the SCORE-15 [28, 29]. The SCORE-15 has been used as a brief measure of family functioning in evaluations of family therapy with populations that share a clinical profile similar to the sample in the current study [53]. An effect size of 0.5 was reported. Similar to above, we conducted a G*Power *t*-test calculation for the difference between two independent means (two groups) for the outcome of family functioning. Assuming *α* = .05, 80% power, two tailed testing, 15% attrition, and 2:1 allocation, the study will need to recruit 144 participants (FT = 96, TAU = 48) to detect a change of 0.5.

These sample sizes should be more than sufficient for mixed model repeated measures (MMRM) across the three time points to have > 80% power and also allow for post hoc *t*-tests both between groups and within groups to have ≥ 80% power.

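### The target of 144 families contains no attrition allowance: after the stated 15% loss, t-test power at d = 0.5 is about 73.5%, not 80%

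*Protocol article*

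**What the plan says.** The Sample size section of the protocol article makes two G*Power calculations for an independent-samples t-test. It says this test was chosen because it should be the least powerful one in the main analysis.

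- **SCORE-15.** The assumed effect comes from earlier family-therapy evaluations: "An effect size of 0.5 was reported". With alpha of 0.05, the conclusion is "80% power, two tailed testing, 15% attrition, and 2:1 allocation, the study will need to recruit 144 participants", split 96 and 48, for an effect of 0.5. The Abstract gives the same 144 (96 and 48) as the number of families to be randomised.
- **SDQ.** With the same alpha, power, attrition and allocation, "the study will need to recruit 38 participants" (25 and 13) for an effect between 0.7 and 1. The text adds that more families will be recruited so that smaller effects can be detected.

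The section ends by saying that these sizes suffice for the mixed model and allow post hoc t-tests "both between groups and within groups to have" at least 80% power. The Recruitment section reports closure on 30 November 2020 and, on the COVID-19 pause, that "we cannot further extend the enrolment period".

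**The concern.** Both sentences list 15% attrition among the inputs, so a reader takes 144 and 38 as already inflated. For d = 0.5 at 2:1 allocation, 144 is the standard uninflated answer. For d = 1, 38 is too. If attrition was listed but never applied, the stated 80% power is available only if no family is lost.

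SCORE-15 is one of two primary outcomes and the one that fixes the trial size. Anyone reading a non-significant SCORE-15 result as an 80%-powered test of d = 0.5 would give it more weight than the design supports. The supposed margin for loss also matters here because the protocol expects COVID-19 to reduce recruitment and possibly retention.

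**Working it through.** **Inputs.** All from the Sample size section: two-sided alpha 0.05, power 80%, allocation 2:1, attrition 15%, d = 0.5 for SCORE-15, d = 0.7 and 1 for SDQ, independent-samples t-test.

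**Formula.** With n1 and n2 families analysed, the noncentrality is δ = d × √(n1·n2/(n1 + n2)) and df = n1 + n2 − 2. Power is the probability that a noncentral t(df, δ) exceeds the 97.5% point of t(df); the other tail is negligible. G*Power uses this method.

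**1. Reproduce 144.** For 96/48: n1·n2/(n1 + n2) = 4608/144 = 32, so δ = 0.5 × 5.657 = 2.828. With df = 142 and critical value 1.977, power is 80.2%. This is the smallest exact 2:1 design reaching 80%; 94/47 gives 79.4%. So 144 is reproduced with **zero** attrition.

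**2. Apply the stated attrition.** 144/0.85 = 169.4, so 170 to recruit, which is 26 more than stated. The cruder 144 × 1.15 gives 166. Other settings do not explain 144: one-sided testing gives 114 before attrition and 135 after, and 1:1 two-sided gives 128 before attrition.

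**3. Power from 144 recruited.** 144 × 0.85 = 122.4, or 81.6 and 40.8 per arm, which round to 82 and 41.
- 82/41: δ = 0.5 × √(3362/123) = 0.5 × 5.228 = 2.614; df = 121; power 73.7%.
- Unrounded 81.6/40.8: power 73.5%.
- Effect detectable with 80% power at 82/41: d = 0.54.

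**4. SDQ figure of 38.**

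| Analysed (FT/TAU) | d = 1 | d = 0.7 |
|---|---|---|
| 25/13, no loss | 81.2% | 51.3% |
| 21/11, after 15% loss | 73.9% | 44.5% |

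At d = 1, 25/12 gives 79.1%, so 38 is the no-loss minimum for d = 1. For d = 0.7, 74 analysed are needed (49/25, power 80.2%), or 75 at an exact 2:1 ratio. Then 74/0.85 = 87.1, so 88 to recruit (89 from 75).

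At the trial's real size after loss (82/41), δ at d = 0.7 is 0.7 × 5.228 = 3.660 and power is 95%.

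**5. Baseline adjustment.** If the baseline correlates r with the 6-month outcome, the effective effect is d/√(1 − r²). At 82/41 and d = 0.5:

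| r (assumed) | Effective d | Power |
|---|---|---|
| 0.3 | 0.524 | 77.6% |
| 0.4 | 0.546 | 80.8% |
| 0.5 | 0.577 | 85.0% |

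The 80% level is reached at r of about 0.38. The protocol gives no value for r.

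**6. If recruitment falls short.** The protocol does not give the number recruited, so these are assumed cases with 15% loss. With 120 recruited, 102 are analysed (68/34) and the effect detectable with 80% power is just under 0.60. With 100 recruited, 85 are analysed (57/28); the detectable effect is 0.65 and power at d = 0.5 is 57%.

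**The case against.** - **The shortfall concerns a deliberately conservative test.** The primary analysis is a mixed model that controls for baseline psychopathology, and a correlation of about 0.38 would bring power back to 80% at 82/41. This stands in part: the claim of more than 80% power for the mixed model is unsupported rather than disproved. It does not rescue the sample-size sentence, because the protocol rests its number on the unadjusted t-test, states no correlation, and makes a separate claim of at least 80% for t-tests.
- **The SDQ figure has no practical effect.** This stands. Nobody planned a trial of 38, and the SDQ comparison keeps about 95% power at d = 0.7. It is a wrong sentence, not a weakness in the design.
- **The t-test claim is not wrong throughout.** Also right. It fails for the between-group SCORE-15 comparison at d = 0.5. It holds for the SDQ at 0.7 to 1 with the real target, and its within-group part was not tested here.
- **The COVID-19 effect on recruitment is disclosed.** It is, and not revising a design-stage calculation for a shortfall of unknown size is no arithmetic error. It only makes the missing margin more relevant.
- **Confidence intervals will show whether 0.5 is excluded.** They will, which limits the harm, but the stated power remains incorrect.
- **144 might mean completers.** This reading is not available: the Sample size section speaks of recruiting 144 and the Abstract of randomising them.

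**Conclusion.** The power statement is wrong as written. The 144 families are the number needed with no loss. Under the protocol's own 15% attrition, the t-test on which the size is based has 73.5% to 73.7% power at d = 0.5, a shortfall of about 6.5 percentage points. Equivalently, it has 80% power for d = 0.54, or 170 families should have been the target. The SDQ figure of 38 has the same omission and does not cover the lower end of its stated range, but this is minor because it does not set the trial size.

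These results rest on the stated inputs, on loss falling equally in both arms, and on one outcome value per family. Power for the baseline-adjusted model may be above or below 80%, depending on a correlation the protocol does not state.

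**What to change.** Recruitment has closed, so the correction is to the text and no more families need be enrolled.

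1. **SCORE-15.** Replace the sentence with wording such as: *Recruiting 144 families (96 and 48) gives 80% power at d = 0.5 only if no family is lost. With 15% attrition (about 82 and 41 analysed) the t-test has about 73.5% power at d = 0.5, or 80% power for d = 0.54.*
2. **SDQ.** Replace with: *38 analysed (25 and 13) detect d = 1 with 80% power; d = 0.7 needs 74 analysed (about 88 recruited). The trial's target exceeds this, with about 95% power at d = 0.7 after 15% loss.*
3. **Post hoc t-tests.** Delete the claim of at least 80% power for between-group tests. Alternatively, base power on the baseline-adjusted 6-month contrast and state the assumed correlation with its source.
4. **Actual recruitment.** Give the detectable effect for the number of families actually recruited and expected to be analysed.

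The cost is a few sentences and a slightly less favourable power figure. No allocation, analysis or data collection changes.
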